#### *10.2. Sample Size Issues*

No statistical sample size estimation was performed as no data are available regarding the safety of rAAV.hCNGA3 (first dose in man) or any other effect in the eye for such a calculation. As three vector dosages are planned in a dose-escalating schedule we decided for three patients in each group. Drop-outs will only be replaced up to a number of two patients in case that other reasons than vector- or procedure-related adverse events are the underlying reasons for the drop-out.

#### *10.3. Definition for Study Groups*

[figure not shown]

Study populations are defined in the following subsections. All populations will be identified and finalized in the Statistical Analysis Plan.

#### **10.3.4. Safety Population**

The Safety Population is defined as all subjects who receive at least one dose of investigational product or corticosteroids and have at least one post-therapy safety assessment.

#### **10.3.5. Intent to Treat Population**

The Intent to Treat (ITT) population is defined as all subjects who are enrolled and received at least one dose of investigational product or corticosteroids, and for whom at least one post-baseline assessment is available.

#### **10.3.6. Per Protocol Population**

The Per Protocol (PP) Population is a subset of the ITT Population and consists of subjects for whom no major protocol violations have been reported. The criteria for defining the PP set will be fully defined in the Statistical Analysis Plan.

A final decision for the allocation to the different populations of the subjects will be made before analysis of trial results.

### ***10.4. Statistical Analysis***

AEs and SAEs will be documented using line listings and tabulations (MetraCad code will be applied). Descriptive analysis will include line charts for individual patients. Standard errors and means will be displayed also using line charts. This will be done for the raw measurements and for the difference between treated and untreated control eye within each patient.

Descriptive parameters will be given for the full cohort (n=9) but not for the sub-cohorts (n=3).

Additionally correlation analysis will be performed in a purely descriptive manner for the comparison of subjective and objective measurements. For each subject and measurement, the delta of the value for the interventional eye minus the mean of control eye values over time will be determined. In scatter plots for pairs of variables (measurements pooled over subjects) the association between these deltas will be displayed.

[figure not shown]

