### 1.3.3. Preclinical testing in non-human primates

Short term (n=12, 28 day) toxicological and long term (n=22, 13 week) toxicology and biodistribution studies were performed in male and female cynomolgus monkeys. The surgical subretinal application procedure proved to be feasible and safe. No ophthalmological adverse events occurred and no serological or clinical adverse events were observed. Animal activity and behavior, ECG and weight were normal up to 13 weeks after subretinal vector administration.

Shedding from the NHP BD studies analyzed in lachrymal and nasal swaps and urine showed detectable DNA in single animals up today 5 (1/6 animals, lachrymal swap), day 7 (nasal swap, 1/6 animals) and day 2 (urine, 1/6 animals) in the low dose subretinal group. Vector DNA could also be identified in single animals up to day 7 (lachrymal swaps, 2/6 animals; nasal swap, 3/6 animals) and day 5 (urine, 2/6 animals) in the high dose subretinal cohort, up to day 7 (lachrymal swap, 1/4 animals; urine, 1/4 animals; nasal swap, 2/4 animals) in the via falsa (intravitreal) high dose cohort. For the majority of animals, at these time-points the number of copies per µg was below or close to the level of significance defined by the FDA (i.e. 100 copies/µg).

None of the animals (which received subretinal injections (either low n=6 or high dose n=6) showed detectable DNA levels in the blood 72h post-injection. In the high dose via falsa group, vector DNA could be identified in the blood of all 4 animals up to four weeks post-injection.

The surgery and the perioperative care in NHPs deviates considerably from the situation in the clinical trial. The instruments available for such a surgery are optimized for human use. Due to the anatomical differences of the eye (e.g. size, location in orbit), some of the safety measures routinely performed in humans were not applicable in the NHPs. For example, displacement of conjunctiva over sclerotomies and introduction of trocars at an oblique angle were not possible. Likewise, NHPs could not be instructed to avoid any manipulation of the eye after

[figure not shown]

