### 7.2. Safety

#### 7.2.1. Ocular and systemic safety

**Safety** as primary endpoint will be assessed by clinical examination of  
*Ocular safety*

3. loss of  $\geq 15$  letters visual acuity at 1m
4. severe, vector-induced, intraocular inflammation unresponsive to treatment

*Systemic safety*

5. vital signs
6. routine clinical chemistry testing (including CRP, IgG, IgM and full/differential blood counts)
7. Immunopathology essays will include specific enzyme-linked immunosorbent assays for humoral antibodies against rAAV8 capsid protein
8. Biodistribution will be monitored by polymerase chain reaction studies on rAAV2/8 genome in blood, urine, saliva and lachrymal fluid.

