#### 8.4.9. PCR of rAAV8 genome

A search for potential systemic rAAV8 virus genome will be performed at early study visits and later on if a control is deemed necessary by the investigator.

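### For vector PCR and anti-AAV8 antibody, the pooled mean and standard error of raw values in section 10.4 is a poor group summary; counts and within-patient fold changes should replace it.

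*Supplement*

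**What the plan says.** Section 7.2.1 lists both items under the primary safety endpoint: "Immunopathology essays will include specific enzyme-linked immunosorbent assays for humoral antibodies against rAAV8 capsid protein" and "Biodistribution will be monitored by polymerase chain reaction studies on rAAV2/8 genome in blood, urine, saliva and lachrymal fluid".

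Section 10.4 plans two displays for measurements. The first is individual: "Descriptive analysis will include line charts for individual patients". The second is a group display: "Standard errors and means will be displayed also using line charts. This will be done for the raw measurements", and likewise for the difference between treated and untreated eye. Descriptive parameters are given for the nine patients together and not by dose cohort. Listings and tables are promised for events only: "AEs and SAEs will be documented using line listings and tabulations".

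Section 10.4 contains no rule for values below detection, no log scale or geometric mean, no fold change from screening, and no count of positive or responding patients. Section 8.4.9 describes the PCR as follows: "A search for potential systemic rAAV8 virus genome will be performed at early study visits", and later if the investigator sees a need. Section 8.4.8 names the capsid ELISA without giving units. Sections 4.2 and 4.3 contain no serostatus criterion.

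**The concern.** Neither item has a fellow-eye value, so the eye-difference half of the group display cannot apply. The only explicit group summary left for them is the mean and standard error of raw values.

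A mean of PCR copy numbers depends on what is entered for non-detects, and it does not say how many patients were positive. A mean of raw antibody levels gives most weight to whoever starts highest, while the safety question is whether each patient rose from his or her own screening value. The reported group result for two primary safety items could then look unremarkable although several patients had changed.

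**Working it through.** The plan states no figure to reproduce: there is no sample size calculation, and nine is 3 cohorts × 3 patients. The check asks how the stated summary behaves at n = 9.

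**How sparse PCR positives may be (section 1.3.3).**
- Blood: 0 of 6 low-dose plus 0 of 6 high-dose subretinal animals were detectable at 72 h, so 0 of 12.
- Low-dose group, which that section equates with the maximum human dose: 1 of 6 positive at the last positive day in lachrymal swab (day 5), nasal swab (day 7) and urine (day 2).
- High-dose group: up to 2 of 6 (lachrymal), 3 of 6 (nasal) and 2 of 6 (urine).
- No saliva result is given.

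**PCR: one positive value x, eight non-detects entered as c.**
- Mean = c + (x − c)/9. SD = (x − c)/3. SE = SD/√9 = (x − c)/9.
- With c = 0, mean = SE = x/9 for every x. For x = 1,000, both are 111.
- With c = 50 (assumed), x = 1,000 gives mean 155.6 and SE 105.6; x = 100 gives mean 55.6 and SE 5.6.
- The same nine results therefore give a mean of 111 or 156 at x = 1,000, depending on a rule that 10.4 does not state.
- Reported as a count, the result is 1/9 = 11% (exact 95% CI 0.3% to 48%). No positives would be 0/9 (0% to 34%). Neither depends on c.

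**Antibody (all levels are assumptions; the documents give none).**
- *Three patients at 100, six at 1; four-fold rise in the six.* Mean before: (300 + 6)/9 = 34.0, SE 16.5. Mean after: (300 + 24)/9 = 36.0, or +6%. Geometric mean fold rise: 4^(6/9) = 2.52.
- *One at 30, eight at 1; four-fold rise in the eight.* Mean before: 38/9 = 4.22, SE 3.2. Mean after: 62/9 = 6.89, or +63%. Geometric mean fold rise: 4^(8/9) = 3.43.
- *One at 10,000, eight at 50; eight-fold rise in the eight.* Mean 1,156 to 1,467, or +27%. Geometric mean fold rise: 8^(8/9) = 6.35.
- *One at 1,000, eight at 50; eight-fold rise in the eight.* Mean 156 to 467, or +200%, with the same geometric mean fold rise of 6.35.

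Across these cases the raw mean moves by 6% to 200%, depending mainly on how high and how many the seropositive values are. As a further illustration, if levels are log-normal with an assumed SD of 0.5 or 1.0 log10, one patient supplies more than half of the nine-patient total in 16.5% or 62% of simulated samples.

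**Denominators.** In the flowchart PCR is fixed only at screening, D3 and D14, and immunopathology only at screening, D30 and D90. Later samples are optional, so a pooled mean at those visits may rest on fewer than nine selected patients.

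**The case against.** The strongest reply is that nothing is concealed. The sentence just before the group summary commits to a chart for each patient, and with nine patients a positive PCR or a multi-fold rise would be seen. This stands. A reader might infer that the plan hides a shedding patient or an antibody response, but the documents do not support that. What the charts lack is a count, and a shared linear axis set by one very high value would flatten a low-level rise.

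Other points also stand in part:
- Section 8.4.9 can be read as detected or not detected, in which case a mean would not arise. The primate results were in copies ("the number of copies per µg was below or close to the level of significance defined by the FDA"), so a quantitative human result is plausible but not stated. Either way, 10.4 names no count. That quoted remark concerns a significance level, not a detection limit, and is not evidence of non-detects.
- Mean = SE holds only if non-detects are entered as zero. Even then a non-zero mean shows that someone was positive.
- The 1-of-6 figures are from the last positive day, so they describe the tail of shedding.
- No ELISA units are given, so the log scale is an assumption. The SE is between patients and is not a yardstick for within-patient change; it is quoted only because it is the bar the chart would draw.
- Section 10.4 also promises unspecified descriptive parameters, and section 10.3 leaves the analysis populations to a separate analysis plan that is not shown. Non-detect rules could sit there. That would not alter the summary 10.4 itself states.
- No decision rests on these means. The stopping rules in 7.4 name neither item, and dose escalation rests on the committee's review of Day 30 safety data.

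**Conclusion.** The point holds for the group summary only. For vector PCR and anti-AAV8 antibody, a pooled mean and standard error of raw values is poorly suited, because PCR is likely to have many non-detects (best supported for blood) and because seropositive patients can enter. The size of the antibody effect rests on assumed levels: it can be near-complete masking (34 to 36 while six of nine patients rise four-fold) or very little (+200%). The individual charts keep the signal visible in the report, and no stopping rule depends on the mean. Severity is low to moderate; the change is worth making because both items belong to the primary endpoint and the remedy costs almost nothing.

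**What to change.** Amend section 10.4 for these two items.

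- **PCR:** replace mean and standard error by number positive over number tested, by sample type and visit. If the assay is quantitative, add the highest copy number and last positive day for each patient, and state how non-detects are shown.
- **Antibody:** report each patient's fold change from screening on a log scale, the geometric mean fold change, and the number of patients above a fold threshold fixed in advance from the assay's repeatability. Show these by screening serostatus.
- **Charts:** keep the individual line charts, with a log axis for these items.

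The cost is analysis wording and a few table rows. All the data are already collected, and no visit or procedure changes.

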## 2. Aim of the Trial

The aim of this phase I trial is to proof the safety and efficacy of rAAV.hCNGA3 at three dosages in patients with achromatopsia.

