### 2.1. Primary Aim

[figure not shown]

The primary aim of the trial is the investigation of the safety of rAAV.hCNGA3 after subretinal injection in patients with CNGA3-linked achromatopsia. Both the ocular and the systemic safety of the intervention will be investigated. Details regarding methods and parameters are described in chapters 7 and 8 of this trial protocol.

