## **3. Study Plan**

### **3.1. Study Design**

This is an open mono-center trial with fellow-eye comparison. Three patients will be assigned to three consecutive, increasing dosage groups (see figure 3):

4) low dose:  $\leq 1 \times 10^{10}$  vgp (n=3)

Between each injection (between patient 1 and 2 and patient 2 and 3) a safety interval of 4 weeks will be kept.

After collection of data on study visit Day 30 of all three patients of the dose cohort and before the scheduled start of the next injections of the consecutive dosage group the DMC will meet and evaluate safety data. If no safety concerns are reported the next dosage group of patients will be treated as scheduled. DMC advice may also result in a dose reduction for the next dosage cohort.

5) intermediate dose:  $\leq 5 \times 10^{10}$  vgp (n=3)

Between each injection (between patient 4 and 5 and patient 5 and 6) a safety interval of 4 weeks will be kept.

After collection of data on study visit Day 30 and before the scheduled start of the next injections of the consecutive dosage group the DMC will meet and evaluate safety data of groups 1 and 2. If no safety concerns are reported the next dosage group of patients will be treated as scheduled. DMC advice may also result in a dose reduction for the next dosage cohort. Within the high dose cohort, the interval between injections / individual patients will be four weeks.

6) high dose:  $\leq 1 \times 10^{11}$  vgp (n=3)

Between each injection (between patient 7 and 8 and patient 8 and 9) a safety interval of 4 weeks will be kept.

The following figure (Fig. 3) explains the schedule and timelines of dose groups and the points of decisions of the data monitoring committee.

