## 10.5. Interim Analyses

An interim analysis is foreseen – beyond those of adverse events for the DMC and annual safety reports – in March/April 2017 in the process of negotiations with industrial sponsors. Those sponsors have an interest in joining the development of rAAV.hCNGA3 and bringing the treatment towards and into a phase III clinical trial.

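### Section 10.4 withholds descriptive parameters for the three dose cohorts and does not commit to showing dose in any safety table, listing or chart, although the trial is a dose escalation

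*Supplement*

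**What the plan says.** The rule is in Section 10.4 of protocol version 5.0, and the synopsis of that version repeats it: "Descriptive parameters will be given for the full cohort (n=9) but not for the sub-cohorts (n=3).

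The same section plans three other kinds of output:

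- AE and SAE line listings and tabulations.
- Line charts for individual patients, and charts of means with standard errors, for raw values and for the treated-minus-fellow-eye difference.
- Scatter plots of paired measurements pooled over subjects.

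For none of these does it say that dose cohort will be shown.

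Section 2 gives the overall aim as "to proof the safety and efficacy of rAAV.hCNGA3 at three dosages in patients with achromatopsia". Section 3.1 sets three consecutive cohorts of three patients, with caps of 1×10^10, 5×10^10 and 1×10^11 vgp. Section 7.2.1 makes safety the primary endpoint. Its ocular part is a loss of 15 letters or more, or severe vector-induced inflammation that does not respond to treatment.

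Section 10.3.4 defines the Safety Population as "all subjects who receive at least one dose of investigational product or corticosteroids and have at least one post-therapy safety assessment". Section 10.3 leaves the final form of the populations to the Statistical Analysis Plan. The supplement contains no separate text of that plan. It says only that the plan did not change apart from the added interim analysis.

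**The concern.** Dose is the only treatment difference that the design builds in between patients. The protocol itself treats dose as relevant to harm. Appendix 1 reports local toxicity in the highest-dose group of a published primate study. It also reports transient reactions in 2 of 4 animals at ten times the trial's maximum dose in the sponsor's own toxicology work. A reader of the final report will therefore first ask whether any harm sits in the top cohort.

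Section 10.4 does not merely leave that detail open. It makes a choice, stated in general terms, to give no descriptive parameters by cohort. If the statistician applies it to safety counts, the report will show totals out of nine and nothing by dose. If the listings and charts also carry no dose label, the reader cannot rebuild the split. A pattern that matters for the choice of dose in later development could then be present in the data and absent from the summary.

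**Working it through.** **Inputs.** Three cohorts of three patients (Section 3.1) and nine patients in total (Section 3.4). Section 10.2 states that no sample size calculation was made, so there is no power figure to reproduce. The total agrees with the design: 3 × 3 = 9. The dose caps span 10^11 / 10^10 = 10-fold, in steps of 5 and 2. These are caps, so the ratio of doses actually given may differ.

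**Method.** Exact two-sided 95% (Clopper-Pearson) limits for x events in n patients are:

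- lower = Beta quantile(0.025; x, n−x+1), or 0 when x = 0
- upper = Beta quantile(0.975; x+1, n−x), or 1 when x = n

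For zero events the upper limit is 1 − 0.025^(1/n).

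| Events / patients | Proportion | Exact 95% limits |
|---|---|---|
| 0/3 | 0% | 0 to 70.8% |
| 1/3 | 33% | 0.8 to 90.6% |
| 3/3 | 100% | 29.2 to 100% |
| 0/9 | 0% | 0 to 33.6% |
| 1/9 | 11% | 0.3 to 48% |
| 3/9 | 33% | 7.5 to 70.1% |

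**What pooling hides in counts.** One event in the high-dose cohort is 1/3 = 33% there and 1/9 = 11% in the pooled table. Three events give 3/9 = 33% whether they fall 1, 1, 1 across the doses or 0, 0, 3.

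These two patterns do not carry the same information. If dose were irrelevant, each of the C(9,3) = 84 ways of placing three events among nine patients would be equally likely:

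- All three in the top cohort: 1 way, probability 1/84 = 1.2%.
- One in each cohort: 3 × 3 × 3 = 27 ways, probability 27/84 = 32%.

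The pooled figure cannot tell them apart. Three x/3 columns can, even at this sample size. The sums only illustrate lost information. No test is proposed.

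**What pooling hides in means.** If an effect of size d exists only at the high dose, the pooled mean is (3×0 + 3×0 + 3×d)/9 = d/3.

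**What n=3 cannot deliver.** The 95% half-width of a mean is t(0.975; n−1)/√n in SD units. It is 4.303/√3 = 2.48 SD at n=3 and 2.306/√9 = 0.77 SD at n=9. Cohort means would be close to uninformative, which supports not reporting them.

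**Safety denominator.** Corticosteroids start on Day −1 (Section 8.4.27) and the vector is given on Day 0. A patient who withdraws in between and has one later safety assessment meets the definition in 10.3.4 without vector exposure. If that patient is replaced, one event reads 1/10 = 10.0% in the Safety Population and 1/9 = 11.1% among those exposed. If not replaced, it reads 1/9 = 11.1% and 1/8 = 12.5%. The shift is small and the case rare.

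**The case against.** Four points on the other side deserve weight.

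1. **Section 10.4 is not pooled throughout.** With nine patients, individual line charts and AE/SAE listings come close to full patient-level reporting. A reader might infer that all results are pooled, but the section does not say so. The exclusion follows the sentences on means and standard errors, while AE tabulations come in an earlier sentence with no such limit. It may never have been meant to cover event counts. This stands, and it is why the point concerns an unlimited rule and missing dose labels.

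2. **Safety is judged by cohort during the trial.** Sections 3.1, 7.2.2 and 7.3.1 require a committee decision on Day 30 data before the second and third cohorts. Section 7.4 lists single events, if attributed to the vector, that discontinue the trial whatever the denominator. This protects patients and stands. It does not replace reporting by dose, however. The scheduled go/no-go decisions follow the low and intermediate cohorts, so none follows the high-dose cohort. Many AEs also fall outside Section 7.4, and for those a cluster of three remains possible.

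3. **The primary aim compares no doses.** Section 2.1 reads: "The primary aim of the trial is the investigation of the safety of rAAV.hCNGA3 after subretinal injection in patients with CNGA3-linked achromatopsia". A reader might infer that the trial cannot answer its own question. That goes too far, since overall safety of the vector can be described from nine patients and their listings. Nor do the documents set any rule by which zero events would count as proof of safety. The verb in Section 2 is a matter of wording, and Section 2.1 speaks of investigation.

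4. **Table layout is often left to an analysis plan not shown here.** Tables by dose defined there cannot be ruled out. But Section 10.4 states a rule against cohort parameters, so a separate plan would have to depart from it or interpret it.

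A reader might also try to count the patients with one-year data at the interim analysis in Section 10.5. The protocol gives neither injection dates nor the visits to be included, so no such count is supported.

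**Conclusion.** The point holds as a mismatch between design and reporting. Section 10.4 excludes dose cohorts from the descriptive parameters without limiting this to means and standard errors, and nothing shown commits any safety output to identifying dose. In size, a single high-dose event goes from 33% to 11% in the summary, an effect confined to the top dose shows at one third of its value, and 3/9 cannot separate an even spread from a cluster at the top dose.

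This assumes that the exclusion may be applied to event counts and that no dose-grouped tables are defined elsewhere. If either assumption fails, what remains is a clarification of wording. The planned individual charts, the listings and the committee's cohort reviews limit the harm, so this is something that should be fixed and not a flaw that defeats the trial. The steroid-only denominator is a real but minor secondary point: Section 10.4 does not name the Safety Population as its denominator, and the circumstance is unlikely.

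**What to change.** In Section 10.4:

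1. Limit the exclusion to means and standard errors for the n=3 cohorts.
2. Tabulate primary safety events, AEs and SAEs as x/3 by dose received, plus the total x/9, with an exact (Clopper-Pearson) 95% interval on the total.
3. Label listings, individual line charts and scatter points by dose cohort.

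In Section 10.3.4, or in the analysis plan that finalises the populations, use vector-exposed patients as the denominator for vector safety and list any steroid-only subject separately.

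The cost is a few more table columns and plot labels. The x/3 counts will be very imprecise (0/3 is compatible with a true risk of up to 70.8%), so the text should say that they are descriptive only and support no comparison between doses. Recruitment, visits, dosing and data collection do not change.
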